**Table 2. Baseline healthcare resource use and productivity losses.**

|  |  | **Costs in Euro** |  |
| --- | --- | --- | --- |
|  | **Posterior Surgery^a^** | **Anterior Surgery** | **Difference (95% CI)** |
| General practitioner | 85 | 82 | -3 (-30 to 23) |
| Physiotherapist | 141 | 199 | 58 (-18 to 135) |
| Company doctor | 31 | 28 | -3 (-20 to 13) |
| Other primary care^b^ | 35 | 38 | 3 (-35 to 41) |
| Care at home | 0 | 44 | 44 (-10 to 98) |
| Neurosurgeon | 122 | 142 | 20 (-9 to 49) |
| Other outpatient clinic visits | 167 | 134 | -33 (-85 to 19) |
| Pain medication | 33 | 31 | -2 (-18 to 15) |
| Emergency department^c^ | 102 | 25 | -77 (-129 to -25) |
| Hospital admissions | 112 | 90 | -23 (-136 to 91) |
| Additional health care costs^d^ | 80 | 192 | 112 (-4 to 228) |
| **Total health care costs** | **998** | **1,223** | **225 (-141 to 591)** |
| Sick leave before surgery, no, (%)  Sick leave > 85 days, no, (%)  Total days of sick leave | 45 (56)  22 (49)  97 | 55 (61)  20 (36)  110 | 13 (-36 to 63) |
| Absenteeism paid work  *Without friction cost method ^e^*  Absenteeism paid work  *With friction cost method* | 3,154  755 | 4,516  2,161 | 1,362 (-837 to 3,561)  1,405 (483 to 2,328) |
| Presenteeism paid work | 2,542 | 1,927 | -614 (-3,262 to 2,034) |
| Absenteeism unpaid work | 274 | 348 | 74 ( -145 to 294) |
| **Total societal costs^f^** | **3,571** | **4,493** | **922 (-1,944 to 3,788)** |

*Abbreviations: Confidence Interval (CI), Number of patients (no.)*

^a^ Percentages may not total 100, because of rounding. Data was missing for 7 (6%) patients in the posterior group and 7 (6%) in the anterior group. Values are presented as mean costs, expressed in rounded Euros.

^b^ Other primary care includes visits to social workers, occupational therapists, speech therapists, dieticians, alternative therapists and psychologists.

^c^ Emergency department includes visits to the emergency department and transportation to the hospital by ambulance.

^d^ Additional health care costs include daycare or admissions to a health institution other than a hospital, rehabilitation Centre or psychiatric institution.

^e^ The ‘friction cost method’ assumes that after a period of 85 days of complete absence, an employee gets replaced by another worker, and productivity would be restored.

**^f^** Total societal costs include absenteeism with the use of the ‘friction cost method”.

**Table 3. Cost differentiation with number of patients reporting costs**

|  | **Posterior Surgery**  **n=119** | **Anterior Surgery**  **n=124** | **Difference (95% CI)** |
| --- | --- | --- | --- |
| General practitioner | 634 | 613 | 28 |
| *n reported* | 71 | 78 |  |
| Physiotherapist  *n reported* | 1,179  50 | 1,450  55 | -355 |
| Company doctor | 158 | 182 | -31 |
| *n reported* | 47 | 41 |  |
| Other primary care^b^  *n reported* | 693  30 | 804  28 | -146 |
| Care at home^c^  *n reported* | 886  0 | 1,450  6 | -739 |
| Neurosurgeon  *n reported* | 338  85 | 298  78 | 52 |
| Other outpatient clinic visits  *n reported* | 734  49 | 1,062  47 | -430 |
| Pain medication  *n reported* | 231  51 | 273  49 | -55 |
| Emergency department^d^  *n reported* | 505  15 | 815  15 | -406 |
| Hospital admissions  *n reported* | 1,612  18 | 2,437  24 | -1,082 |
| Additional health care costs^e^  *n reported* | 1,693  40 | 1,991  45 | -391 |
| **Total health care costs** | **12,248** | **16,055** | **-3,807 (-6,580 to -1,127)** |
|  |  |  |  |
| Absenteeism paid work^f^  *n reported* | 8,708  43 | 8,818  40 | -110 |
| Presenteeism paid work^f^  *n reported* | 2,434  25 | 560  18 | 1,874 |
| Absenteeism unpaid work^f^  *n reported* | 4,655  64 | 4,653  53 | 2 |
| **Total productivity losses**  **Total societal costs** | **15,797**  **28,046** | **14,031**  **30,086** | **1,767 (-5,358 to 8,373)**  **-2,674 (-19,603 to 5,547)** |

*Abbreviations: Confidence Interval (CI), Standard deviation (SD), number (n)*

*Values are presented as pooled estimated means in rounded Euros. ‘N reported’ are the number of patients that reported costs for a certain subcategory in the original data set.

^a^ Surgical costs include the price for the procedure, implants and haemostatics, and costs for days of admission to the hospital for the initial intervention.

^b^ Other primary care includes visits to social workers, occupational therapists, speech therapists, dieticians, alternative therapists and psychologists.

^c^ Care at home was not reported by any of the patients in the posterior group, to note is that the reported costs are estimated pooled means, using multiple imputation and bootstrapping.

^d^ Emergency department includes visits to the emergency department and transportation to the hospital by ambulance.

^e^ Additional health care costs include day-care or admissions to a health institution other than a hospital, rehabilitation centre or psychiatric institution.

^f^ Absenteeism is the amount of days that a patient was absent from work times the Dutch reference wage per day. The ‘friction cost method’ was applied, assuming that after a period of 85 days of complete absence, an employee gets replaced by another worker, and productivity would be restored. Presenteeism is the loss of productivity by patients that were not able to fully fulfil their jobs. It was calculated by the proportion of productivity loss of a general working day, times the duration in days, times the average wage per day. Unpaid work is the loss of productivity during unpaid activities such as household work and volunteering. It was calculated by hours a day, times the duration in days, times the Dutch reference price for one hour of unpaid work.

**
[figure not shown]
Figure 1.** **Incremental Cost-Effectiveness Plane comparing Cost Difference and Neck Disability Index from a Societal Perspective.**

*Abbreviations: Multiple imputation sets (MI).*

Figure 1 depicts the cost difference of posterior versus anterior surgery on the vertical axis in Euros, and the difference in Neck Disability Index (NDI) score between groups on the horizontal axis.

**
[figure not shown]
Figure 2. Incremental Cost-Effectiveness Plane comparing Cost Difference and Neck Disability Index from a Healthcare Perspective.**

*Abbreviations: Multiple imputation sets (MI).*

Figure 2 depicts the cost difference of posterior versus anterior surgery on the vertical axis in Euros, and the difference in Neck Disability Index (NDI) score between groups on the horizontal axis.

**
[figure not shown]
Figure 3. Incremental Cost-Effectiveness Plane comparing Cost Difference and Odom Criteria from a Societal Perspective.**

Figure 3 depicts the cost difference of posterior versus anterior surgery on the vertical axis in Euros, and the difference in proportion of Successful Odom Scores between groups on the horizontal axis. A successful Odom score is the proportion of patients graded ‘excellent’ or ‘good’ on the modified Odom criteria, based on patients with complete cost data for all time points and an available Odom score (n=80 in the posterior group and n=73 in the anterior group).

**
[figure not shown]
Figure 4. Incremental Cost-Effectiveness Plane comparing Cost Difference and Odom Criteria from a Healthcare Perspective.**

Figure 4 depicts the cost difference of posterior versus anterior surgery on the vertical axis in Euros, and the difference in proportion of Successful Odom Scores between groups on the horizontal axis. A successful Odom score is the proportion of patients graded ‘excellent’ or ‘good’ on the modified Odom criteria, based on patients with complete cost data for all time points and an available Odom score (n=80 in the posterior group and n=73 in the anterior group).

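### Supplementary Table 3 prints a societal cost difference of -2,674 where its own totals give -2,040; 11 component differences share the same factor of about 1.31, and the societal interval does not fit its components

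*Combined protocol and SAP*

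**What the plan says.** Supplementary Table 3 lists costs by arm (posterior n=119, anterior n=124) with a difference column, posterior minus anterior. Its note says "Values are presented as pooled estimated means in rounded Euros". The three totals are:

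- Healthcare: 12,248 and 16,055, difference (printed negative) "3,807 (-6,580 to -1,127".
- Productivity: 15,797 and 14,031, difference "1,767 (-5,358 to 8,373".
- Societal: 28,046 and 30,086, difference (printed negative) "2,674 (-19,603 to 5,547".

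Two of the 11 healthcare component rows read "General practitioner | 634 | 613 | 28" and "Company doctor | 158 | 182 | -31".

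Supplementary Table 2 gives baseline costs with differences taken the other way round (anterior minus posterior). Its societal totals are 3,571 and 4,493, with difference "922 (-1,944 to 3,788".

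The cost-effectiveness section of the protocol's statistical analysis chapter takes a societal perspective and plans two incremental ratios plus acceptability curves from bootstrap simulations.

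**The concern.** A difference column should equal the difference of the two columns beside it, within rounding. In Table 3 it does so for some rows and not for others, and the societal total is among those that fail. That row is the cost contrast for the perspective the protocol chose. A reader who takes it at face value sees a larger mean saving than the arm totals support. The interval also suggests far more room on the saving side than the two component intervals allow. If the same values went into the ratios or the societal planes, the error would travel with them.

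**Working it through.** **Inputs.** All come from Supplementary Table 3 unless stated, in euros.

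**1. Rows that reproduce (posterior minus anterior).**
- Healthcare total: 12,248 - 16,055 = -3,807, as printed.
- Paid absenteeism: 8,708 - 8,818 = -110. Presenteeism: 2,434 - 560 = 1,874. Unpaid work: 4,655 - 4,653 = 2. All as printed.
- Productivity total: 15,797 - 14,031 = 1,766, printed 1,767 (rounding).

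**2. Societal difference.**
- From the totals: 28,046 - 30,086 = -2,040.
- From the subtotals: -3,807 + 1,767 = -2,040.
- Printed: -2,674. Gap 634; 634 / 2,040 = 31%; ratio 2,674 / 2,040 = 1.311.

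**3. Healthcare components.**

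| Row | From columns | Printed | Ratio |
|---|---|---|---|
| General practitioner | 21 | 28 | 1.33 |
| Physiotherapist | -271 | -355 | 1.31 |
| Company doctor | -24 | -31 | 1.29 |
| Other primary care | -111 | -146 | 1.32 |
| Care at home | -564 | -739 | 1.31 |
| Neurosurgeon | 40 | 52 | 1.30 |
| Other outpatient | -328 | -430 | 1.31 |
| Pain medication | -42 | -55 | 1.31 |
| Emergency department | -310 | -406 | 1.31 |
| Hospital admissions | -825 | -1,082 | 1.31 |
| Additional care | -298 | -391 | 1.31 |
| Sum | -2,712 | -3,555 | 1.31 |

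Each entry misses by more than rounding allows. With each arm mean and each difference rounded to the nearest euro, a single factor between 1.310 and 1.312 fits all 11 rows and the societal total.

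The listed rows sum to 8,663 and 11,375, so the healthcare totals leave 3,585 and 4,680. A footnote defines surgical costs, for which no row appears in the text available. That remainder is therefore not counted as an error.

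**4. Societal interval.** Write W for the width of a 95% interval. Under approximate normality the width for a sum is W² = W1² + W2² + 2ρW1W2, where ρ is the correlation, and it cannot exceed W1 + W2.
- Healthcare: W1 = 6,580 - 1,127 = 5,453.
- Productivity: W2 = 8,373 + 5,358 = 13,731.
- Maximum for the sum (ρ = 1): 19,184. At ρ = 0: √(5,453² + 13,731²) = 14,774.
- Printed: 5,547 + 19,603 = 25,150, which would need ρ = 2.77.
- Lower limits added: -6,580 - 5,358 = -11,938. The printed lower limit is 19,603 - 11,938 = 7,665 below that.
- Printed midpoint: (-19,603 + 5,547) / 2 = -7,028, far from both -2,040 and -2,674.
- Centred on -2,040, the interval would run from about -9,427 to 5,347 at ρ = 0, and from -11,632 to 7,552 at ρ = 1.
- Trial value -9,603 for the lower limit: width 15,150, midpoint -2,028, implied ρ = 0.08.

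**5. Table 2.**
- Posterior: 755 + 2,542 + 274 = 3,571, the printed societal total exactly, with no healthcare in it. In Table 3 the same label includes healthcare (12,248 + 15,797 = 28,045, printed 28,046).
- Anterior: 2,161 + 1,927 + 348 = 4,436, printed 4,493 (57 apart).
- Healthcare rows sum to 908 and 1,005; the printed totals are 998 and 1,223.
- Sick leave of 45 (56%) and 55 (61%) implies about 80 and 90 patients, while the arm sizes less the missing patients are 119 - 7 = 112 and 124 - 7 = 117.

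**The case against.** **Pooling might explain the differences.** The entries come from multiple imputation and bootstrapping, so small departures from subtraction could arise. But an unadjusted difference pooled over imputations equals the difference of the pooled means. Covariate adjustment would not multiply 11 separate items by one factor and leave the productivity rows exact. The documents give no explanation, and the cause cannot be established from them.

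**A bootstrap interval need not obey a normal-theory bound.** This is true, and no interval can be derived from columns of means. What can be said is that the societal interval conflicts with its components. Those components are close to symmetric (2,773 and 2,680 either side of the estimate for healthcare, 7,125 and 6,606 for productivity), which leaves little room for skew as the explanation. The 1.31 factor does not rescue the interval either. Dividing by 1.311 gives about -14,950 to 4,230, which is about as wide as the bound (19,184) but centred near -5,360, with a lower limit still some 3,000 below -11,938.

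**Stronger readings that a reader might infer, and that the documents do not support.**
- That the lower limit is EUR 10,000 too low. This rests on a guessed extra digit. The value -9,603 fits well, but fit is not proof.
- That the imputed home-care cost is a further error. The table's own footnote discloses that "Care at home was not reported by any of the patients in the posterior group" and that the EUR 886 is a pooled estimate. Not reporting use is not the same as not using care. Forcing the arm to zero would assume that every patient with missing data had none, and the imputation model is not described.
- That Table 2's societal totals should be 4,569 and 5,659, found by adding healthcare. The healthcare totals to be added do not match their own rows, the anterior sum is 57 off, and the rows may not share a denominator. The row could equally be mislabelled; its difference of 922 does agree with its columns.

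**Conclusion.** The concern holds for Table 3. The societal difference should read -2,040 on the scale of the arm columns, so the printed saving is EUR 634 (31%) too large. Eleven healthcare component differences share the same inflation of about 1.31. This part rests on subtraction alone. The finding on the interval assumes approximate normality: the printed width exceeds the maximum by 25,150 - 19,184 = 5,966, and the lower limit is implausible. The correct limits cannot be found without the bootstrap output.

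The consequence is limited. The direction is unchanged, and the printed and plausible intervals all include zero. The healthcare and productivity totals stand. A reader might infer that the cost-effectiveness ratios or planes are wrong, but nothing in the documents shows that -2,674 or its interval fed them. These are reported results in a supplement, so the trial's design and sample size are not affected.

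Table 2 is a secondary matter. It contains inconsistencies that need reconciling, but no replacement figures can be given.

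**What to change.** - In Table 3, restate the 11 healthcare component differences and the societal difference on the scale of the arm columns, using the values in the working (societal -2,040). If another scale was intended, say so and explain why the other rows do not use it.
- Check the societal interval against the bootstrap output and correct it. This may be a single digit or a regenerated interval; the output will show which.
- Confirm which societal differences fed the cost-effectiveness ratios and the societal planes (Supplementary Figures 1 and 3), and correct any that used the inflated values.
- In Table 2, reconcile the societal and healthcare totals with their rows, correct or relabel them so that the societal label means the same in both tables, and state the denominator of each block.
- Optionally, check whether the imputed EUR 886 for posterior care at home is plausible. No re-imputation is required on this evidence.

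No new data are needed. The cost is a check of the stored analysis output, corrected tables and a smaller stated saving.
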